### Safety monitoring

We will monitor potential harm from study treatments experienced by participants by recording the occurrence of adverse (AE) and serious adverse events (SAE). Any AE and SAE experienced by participants after consenting to the study will be recorded and reported regardless of whether it is likely that they are the result of treatment received. The Health Research Authority defines SAE as an occurrence that (a) results in death, (b) is life-threatening, (c) requires hospitalization or prolongation of existing hospitalization, (d) results in persistent or significant disability or incapacity, and (e) consists of a congenital anomaly or birth defect. Applying this definition to psychiatric inpatient settings, acts of serious self-harm, attempted suicide, and suicide would qualify as a SAE. Events that constitute SAEs are already routinely collected and monitored at all participating sites using the Datix incident reporting software.

AEs will be similarly monitored throughout the study. In the present study, an AE is considered to have occurred if either of the following takes place: (a) participant is removed from the study at the request of their RMO due to significant deterioration in the patient’s mental state and/or behavior and (b) a participant’s global CORE-OM score (indexes overall psychiatric distress) increases from the previous assessment to an extent that is both clinically significant and reliable (as defined in Evans et al. [19]). All SAEs and AEs will be recorded, and SAEs will be reported to a NHS Scotland Research Ethics Committee if and when they occur.

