### Data collection and outcome measures

#### Participant timeline

The trial consists of a 12-week treatment phase with a 3-month (13-week) follow-up phase. As shown in Fig. 1, participants in both treatment conditions will be assessed pretreatment at T0, post treatment at T1, and 3-months after post-treatment at T2. A schedule of study procedures and assessments is detailed in Table 1.

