#### Primary outcome measures

Primary study outcomes relate to the feasibility and acceptability of key trial procedures.Number of eligible participants identified over the study period will be indexed by the total number of participants identified across sites who meet eligibility criteria.Estimate rate of recruitment into the trialThe proportion of eligible patients who agree to participate (provide consent): We anticipate the consent refusal rate to fall in the range of 16–37% based on findings from previous RCTs of psychological interventions in forensic populations [21–24]. The adopted benchmark of success in this study is a consent refusal rate in this study of less than 37%.The number of participants enrolled into the study each month during the recruitment period: As in other ongoing feasibility RCTs [25], the benchmark of recruitment success is achieving 80% of target sample size, in this case recruiting at least 40 participants into the study.Audit adherence to randomization procedure: The number of instances where the actual treatment allocation differed from assigned allocation. Instances where the participant is removed from the study by his or her RMO, who cites a reason related to the allocated condition as opposed to deterioration in clinical presentation, will also be considered non-adherence to the randomization process. Any instances of non-adherence to the randomization procedure will cause great concern as to the feasibility of a future phase III RCT of OTRTR.Estimate completion rate of OTRTR: Proportion of participants who complete OTRTR. Following similar studies [26, 27] participants will be considered to have completed OTRTR if they attended at least 80% of the planned sessions.Explore reasons for study drop-out during the study treatment: Participants will have the option of providing a reason they do not wish to continue with the study before exiting the study.Completion rate of primary clinical outcome measures weekly during treatment phase: The proportion of Birchwood Insight Scale (BIS) and Coping Styles Questionnaire (CSQ) forms completed as intended each week during the treatment phase will be calculated.Completion rate of standardized recording forms of the therapy content delivered by OTRTR therapy facilitators: Proportion of complete forms will be calculated.Number of participants lost to follow-up and reasons: Number of participants who withdrew from the study or who were otherwise lost to follow-up, with reasons recorded (if provided). The adopted benchmark of success is a participant attrition rate of less than 20% at the post-treatment (T1) assessment.Safety of OTRTR for patients: Descriptive statistics for frequency of observed AEs and SAEs across treatment conditions. Adverse events may occur for reasons independent of the therapy being studied due to the nature of this clinical population. Safety of OTRTR will be assessed by comparing the rates of SAEs and AEs across the two study treatment conditions. We will also compare the incident rate of SAEs for study participants to the rate observed for each participant in the 12 weeks prior to enrolment in the study. This reference data will be requested from the local site clinical effectiveness departments or equivalents following study completion.Average duration of assessment battery at T0, T1, and T2. Descriptive statistics for length of assessment. We anticipate the T0 assessment will last approximately 90 min, and the T1 and T2 assessments 60 min each.

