#### Secondary outcomes

The secondary outcome measures relate to intended treatment outcomes of OTRTR. The following measures will be completed at baseline (T0), post treatment (T1), and 3-month follow-up (T2) by a researcher blind to the participant’s allocation status.Birchwood Insight Scale (BIS) [14] is an eight-item self-report measure of insight. The original study established BIS total score test-retest reliability (1-week) as *r* = 0.90 and internal consistency of *α* = 0.75. The BIS variable used in this study will be the total score (max 12).Coping Styles Questionnaire (CSQ) [15] is a 60-item self-report measure on the use of maladaptive and adaptive coping styles. It is comprised of four subscales, each a unique dimension of coping: rational, detached, emotional, and avoidance. Test-retest reliability of the CSQ subscales range from *r =* 0.70 to 0.80, and the subscale internal consistencies of *α* = 0.69 to 0.90. The CSQ variable used in this study will be the total of the two adaptive coping subscales, Rational and Detached.Clinical Outcomes in Routine Evaluation Outcome Measure (*CORE-OM*) [28] is a 34-item self-report measure of psychological distress that covers four domains: wellbeing, symptoms/problems, functioning, and risk to self and others. A global measure of distress is also calculated across these domains. Good psychometric properties for this measure in non-clinical, clinical, and forensic populations have been established [19, 29]. The CORE-OM variable used in this study will be the 34-item mean score (max 4).Rosenberg Self-Esteem Scale (RSE) [30] is a 10-item self-report measure of self-esteem. The RSE has an internal consistency of *α* = 0.77 and two-week test-retest reliability of *r* = 0.85. The total RSE score will be used (max 30).Questionnaire on the Process of Recovery (QPR) [31] is a 22-item measure of service user-rated recovery comprised of an interpersonal and intrapersonal subscale. The initial validation study found acceptable two-week test-retest reliability (intrapersonal subscale *r* = 0.87, interpersonal subscale *r* = 0.77) and internal consistency (intrapersonal *α* = 0.94, interpersonal *α* = 0.77). The intrapersonal (max 68) and interpersonal (max 20) subscale scores will be used.Brief Psychiatric Rating Scale (BPRS) [32] is a clinician/researcher-rated tool used to assess severity of psychopathology. The 18 items sum to derive a continuous total score of symptom severity. The BPRS has good psychometric properties is the most widely used outcome measure in treatment studies across populations with severe and persistent mental illness [33]. The total BPRS score will be used (max 126).Institution-recorded incidents of physical aggression and violence: The number of incidents of violence/aggression, for which the participants are considered to have responsibility in instigating or exacerbating, during the study treatment phase and 3-month follow-up period will be compared across treatment groups. This information will be as participants complete T2.Institutional privileges: Changes in institutional privileges (e.g., increased grounds access, unsupervised phone calls, and patient outings) will be recorded for all participants during the study treatment phase and 3-month follow-up period. This information will be after participants complete T2.

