#### Clinical outcomes

This study will not be sufficiently powered to determine treatment efficacy. Evidence of change on clinical outcomes will be considered with a focus on effect sizes and reliable change indices over null hypothesis significance testing. Effect size estimates (Cohens’ *d*) will inform sample size estimates and inform decisions regarding the most appropriate outcome measures for use in a future phase III trial of OTRTR. A modified intention to treat (ITT) analysis will be used to analyze change on the outcome measures and derive the effect size estimates. Therapeutic effect sizes (with 95% confidence intervals) will be derived using linear regression models comparing T1 scores for the two treatment arms, with baseline (T0) scores included as covariates. These analyses will be repeated using between-group comparison of means at T2 for estimated maintenance of treatment effects.

Similarly, effect sizes for change in institutional violence/aggression will be derived. The mean number of incidents of violence/aggression (recorded by the institution) measured at post treatment (the mean number of incidents for duration of study treatment phase, up to T1) will be compared, controlling for baseline differences (the mean number of incidents for the 3-months preceding treatment, up to T0). This analysis will be repeated using between-group comparison of mean incidents during follow-up period (record from T1 to T2) for estimated maintenance of treatment effect.

Changes in institutional privileges (e.g., increased grounds access, unsupervised phone calls, and patient outings) will be recorded for participants in both groups throughout the study treatment phase (T0 to T1) and follow-up period (T1 to T2). To the researchers’ knowledge, this type of outcome has not been previously studied in treatment evaluations in forensic settings. This data will be examined primarily to identify the types of changes that occur and will be used to inform secondary outcome measure selection and refinement in a future definitive RCT. Descriptive statistics will be calculated and examined.

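### At T2 the CORE-OM adverse-event rule is measured from T1, so complete loss of an earlier gain can count as harm and bias the between-arm safety comparison against OTRTR

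*Protocol article*

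**What the plan says.** Safety monitoring gives two AE criteria. Criterion (b) is met when the global CORE-OM score "increases from the previous assessment to an extent that is both clinically significant and reliable", with the definition taken from a cited source. AEs "will be recorded and reported regardless of whether it is likely that they are the result of treatment received".

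Participants in both arms are "assessed pretreatment at T0, post treatment at T1, and 3-months after post-treatment at T2", and Table 1 lists CORE-OM at those three visits only. The reference is therefore T0 for the T1 score and T1 for the T2 score.

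Primary outcome measures lists safety among the primary outcomes and states how it is judged: "Safety of OTRTR will be assessed by comparing the rates of SAEs and AEs across the two study treatment conditions". The article gives no version of the count measured from T0 and no rule for a score that rebounds to its entry level.

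Clinical outcomes foresees that a benefit may not last: "These analyses will be repeated using between-group comparison of means at T2 for estimated maintenance of treatment effects".

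**The concern.** A between-arm comparison of harm needs a reference point that allocation cannot move. T0 meets that condition; T1 does not. One OTRTR module aims to build skills for managing distress, and CORE-OM measures distress. If the therapy works, it lowers the score that becomes the yardstick for harm three months later. Using the same rule in both arms does not cure this, because the yardstick itself differs by arm.

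At stake is the reading of the AE table. Loss of a gain and deterioration below the entry state are different findings for the design of a definitive trial, and the T2 count does not separate them. The rule can also err the other way. Two rises that each fall short of the threshold, one from T0 to T1 and one from T1 to T2, may add up to a reliable worsening from entry and never be counted.

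**Working it through.** The protocol states no AE rate, CORE-OM SD, reliability or cut-off, so there is no figure of its own to reproduce. From the document come the reference rule, the three visits, the 0 to 4 score range and 25 participants per arm. Everything else below is an assumption.

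**1. Closed form for the T2 interval alone.** Scores are in SD units, with correlation r between visits, TAU stable, and OTRTR better by d at T1 and back to its T0 level at T2.
- Reliable-change limit: L = 1.96 × √(2(1 − reliability)). With reliability 0.90, L = 1.96 × √0.2 = 0.877.
- SD of change: s = √(2(1 − r)). With r = 0.7, s = √0.6 = 0.775.
- TAU: P(z > 0.877/0.775) = P(z > 1.13) = 12.9%.
- OTRTR with d = 0.5: P(z > (0.877 − 0.5)/0.775) = P(z > 0.49) = 31.3%. The ratio is 2.4.
- Over d 0.3 or 0.5, r 0.6 to 0.8 and reliability 0.85 or 0.90 (12 settings), the T2 ratio runs from 1.6 to 4.1.

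**2. Both intervals together.** The safety comparison does not single out T2, and a real benefit reduces T0-to-T1 events in OTRTR. The proportion with any CORE-OM AE, simulated over the same 12 settings, gives these OTRTR/TAU ratios:

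| Benefit at T2 | Ratio under the written rule |
|---|---|
| Wholly lost | 1.1 to 2.1 |
| Half lost | 0.93 to 1.15 (below 1 in nine settings, 1.00 in one, above 1 in two) |
| Maintained | 0.57 to 0.79 |

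**3. A second model that also requires crossing a cut-off.** Scores are held to 0 to 4 with SD 0.7. Mean 0.7 to 1.7, r 0.6 or 0.8, d 0.2, 0.5 or 0.8, reliable change 0.4 to 0.87 and cut-off 1.0 or 1.3 were varied.
- Wholly lost: T2 AEs are higher in OTRTR in all 192 scenarios, by 0.9 to 23.0 percentage points. With both intervals combined, the OTRTR minus TAU difference is −0.9 to +2.0 points at d = 0.2, −0.9 to +7.8 at d = 0.5, and +0.1 to +17.8 at d = 0.8.
- Half lost: the combined count is higher in OTRTR in 9%, 42% and 55% of scenarios at d = 0.2, 0.5 and 0.8.

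**4. One worked example from that model**, with the benefit wholly lost (mean 1.3, r 0.8, d 0.5, reliable change 0.5, cut-off 1.2):

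| | OTRTR | TAU |
|---|---|---|
| AE at T1 | 1.0% | 5.2% |
| AE at T2, measured from T1 | 16.4% | 5.3% |
| Any AE, written rule | 17.5% | 10.4% |
| AE at T2 with score at or below own T0 | 4.2% | 0.9% |
| AE at T2, measured from T0 | 5.3% | 5.3% |
| Any AE, measured from T0 | 5.8% | 8.7% |

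Per 25 participants the written rule gives 0.175 × 25 = 4.4 against 0.104 × 25 = 2.6, a gap of about two. At T2 the gap of 16.4 − 5.3 = 11.1 points disappears when the same scores are measured from T0.

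**5. The missed case.** With L = 0.877 SD, two successive rises of 0.6 SD are each below the limit. Their sum, 1.2 SD, is above it. On the reliability criterion, neither visit would be flagged.

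**The case against.** A reliable and clinically significant rise in distress after therapy ends is a proper event to record, whatever the participant's entry score, and the protocol chooses to record events irrespective of cause. That stands, and it is why such rises should not be dropped from AE recording.

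A reader might infer that anyone who merely returns to the entry level is scored as harmed. The text does not support that, because the rise must be both reliable and clinically significant. A lost gain of 0.3 to 0.5 SD is by itself below the assumed limit of 0.88 to 1.07 SD. In the closed-form example only about 8 of the 31 points of OTRTR T2 events fall in participants at or below their own T0 score.

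A reader might also infer that any therapy with a fading benefit will show more AEs than TAU. That is not general either: the excess depends on the benefit being wholly, or almost wholly, lost. Nor does the change of direction in the worked example prove that the T0-referenced result is the true one. Under full loss the T2 rates measured from T0 are equal by construction, and the lower OTRTR total comes from the benefit at T1.

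The consequence is bounded. The AE analysis is descriptive, the progression criteria contain no AE threshold, and the planned CORE-OM comparisons at T1 and T2 would let a reader see a lost gain. None of this removes the dependence of the T2 yardstick on allocation.

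**Conclusion.** The point holds as a conditional bias. At T2, criterion (b) uses a post-randomization reference, so loss of an earlier gain can be counted as harm in a comparison that serves a listed primary outcome.

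If the OTRTR benefit is wholly lost by T2, the proportion with any CORE-OM AE is about 1.1 to 2.1 times TAU, which is about two extra participants per 25 in the worked example. With half the benefit lost the total is often equal to or below TAU; with the benefit maintained it is below TAU. The rule can also miss gradual worsening from entry.

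All magnitudes rest on assumed SDs, reliabilities, correlations, effect sizes and cut-offs, and on clinical significance meaning a crossed cut-off wherever that was modelled. The cited definition is not in the document. The structural point needs none of these figures. With so few events expected, a shift of two participants could change how the safety table is read.

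**What to change.** In Safety monitoring, keep recording every rise from the previous assessment that meets criterion (b) as an AE for individual monitoring. In Primary outcome measures, state that the between-arm CORE-OM safety comparison is based on a reliable and clinically significant increase from T0, assessed at T1 and again at T2. Beside it, report T0-to-T1 and T1-to-T2 AEs separately by arm, and show how many T2 events are in participants at or below their own T0 score.

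This uses scores already collected and also catches two sub-threshold rises that add up to worsening from entry. The cost is about one sentence and one extra table. The downside is that a T1-to-T2 rise ending at or below the T0 level appears in the interval table and not in the T0-referenced rate.

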### Data collection and outcome measures

#### Participant timeline

The trial consists of a 12-week treatment phase with a 3-month (13-week) follow-up phase. As shown in Fig. 1, participants in both treatment conditions will be assessed pretreatment at T0, post treatment at T1, and 3-months after post-treatment at T2. A schedule of study procedures and assessments is detailed in Table 1.

**Fig. 1 Fig1:**
[figure not shown]
Participant flow diagram

**Table 1 Tab1:** Schedule of study procedures and assessments

	Study period						
	Recruitment	Baseline (T0)	Allocation	Treatment phase	Post treatment (T1)	3-month follow-up (T2)	Post-study Interview (optional)
Procedures							
Eligibility screen	X						
Assess capacity	X						
Informed consent	X						
Randomization			X				
Assessments							
Birchwood Insight Scale (BIS)		X		X (weekly)	X	X	
Coping Styles Questionnaire (CSQ)		X		X (weekly)	X	X	
Clinical Outcomes in Routine Evaluation (CORE-OM)		X			X	X	
Rosenberg Self-Esteem Scale (RSE)		X			X	X	
Questionnaire on the Process of Recovery (QPR)		X			X	X	
Brief Psychiatric Rating Scale (BPRS)		X			X	X	
Letter-Number Sequencing Test (LNST)		X			X	X	
Study entrance questionnaire		X					
Post-study interview							X
Intervention							
On the Road to Recovery				X			
Treatment as usual				X			

#### Baseline measures

The following measures will be collected at T0. They will be used as moderator variables in analysis to identify mechanisms of change and predict therapy outcomes at the individual level. We will explore the associations between these variables and change on the clinical outcome measures from T0 to T1.Demographic data (age, sex, ethnicity, education level)Primary and secondary psychiatric diagnosesMedication at each assessment pointPrevious participation in psychological therapiesTime since admission (months)*Verbal working memory*: The Letter-Number Sequencing subtest of the WAIS-IV [20] will be used to index verbal working memory. Working memory was identified as one of several cognitive abilities which may impact patients’ ability to engage with and benefit from the On the Road to Recovery intervention.

#### Primary outcome measures

Primary study outcomes relate to the feasibility and acceptability of key trial procedures.Number of eligible participants identified over the study period will be indexed by the total number of participants identified across sites who meet eligibility criteria.Estimate rate of recruitment into the trialThe proportion of eligible patients who agree to participate (provide consent): We anticipate the consent refusal rate to fall in the range of 16–37% based on findings from previous RCTs of psychological interventions in forensic populations [21–24]. The adopted benchmark of success in this study is a consent refusal rate in this study of less than 37%.The number of participants enrolled into the study each month during the recruitment period: As in other ongoing feasibility RCTs [25], the benchmark of recruitment success is achieving 80% of target sample size, in this case recruiting at least 40 participants into the study.Audit adherence to randomization procedure: The number of instances where the actual treatment allocation differed from assigned allocation. Instances where the participant is removed from the study by his or her RMO, who cites a reason related to the allocated condition as opposed to deterioration in clinical presentation, will also be considered non-adherence to the randomization process. Any instances of non-adherence to the randomization procedure will cause great concern as to the feasibility of a future phase III RCT of OTRTR.Estimate completion rate of OTRTR: Proportion of participants who complete OTRTR. Following similar studies [26, 27] participants will be considered to have completed OTRTR if they attended at least 80% of the planned sessions.Explore reasons for study drop-out during the study treatment: Participants will have the option of providing a reason they do not wish to continue with the study before exiting the study.Completion rate of primary clinical outcome measures weekly during treatment phase: The proportion of Birchwood Insight Scale (BIS) and Coping Styles Questionnaire (CSQ) forms completed as intended each week during the treatment phase will be calculated.Completion rate of standardized recording forms of the therapy content delivered by OTRTR therapy facilitators: Proportion of complete forms will be calculated.Number of participants lost to follow-up and reasons: Number of participants who withdrew from the study or who were otherwise lost to follow-up, with reasons recorded (if provided). The adopted benchmark of success is a participant attrition rate of less than 20% at the post-treatment (T1) assessment.Safety of OTRTR for patients: Descriptive statistics for frequency of observed AEs and SAEs across treatment conditions. Adverse events may occur for reasons independent of the therapy being studied due to the nature of this clinical population. Safety of OTRTR will be assessed by comparing the rates of SAEs and AEs across the two study treatment conditions. We will also compare the incident rate of SAEs for study participants to the rate observed for each participant in the 12 weeks prior to enrolment in the study. This reference data will be requested from the local site clinical effectiveness departments or equivalents following study completion.Average duration of assessment battery at T0, T1, and T2. Descriptive statistics for length of assessment. We anticipate the T0 assessment will last approximately 90 min, and the T1 and T2 assessments 60 min each.

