### Description of the intervention

#### On the Road to Recovery

The OTRTR program is comprised of two brief treatment modules: *Awareness & Recovery* (A&R) and *Looking After Yourself* (LAY). A&R provides psychoeducational material adapted from Morrison et al. [16] “Think you’re crazy? Think Again” and from “Coping with Mental Illness” [17], the original psychoeducation program delivered across the Forensic Network. The LAY program’s core aim is to help patients develop basic coping skills to manage psychological distress and to develop a “toolkit” for coping with this distress now and in the future. The protocol is semi-structured and organized by topics instead of sessions, which allows the program to flexibly match pace to groups with greater or lesser need by adjusting the number of sessions. Each topic contains several objectives that are accompanied by structured didactic activities, exercises, and discussion prompts. The program will run over approximately 12 weeks, with weekly 2-h sessions. Treatment delivery is primarily in small groups; however, the program can also be delivered on an individual basis as part of the study. Participant attendance and engagement in the treatment sessions will be monitored and recorded. Participants’ RMOs may withdraw a participant from the study and therefore discontinue OTRTR sessions should there be a deterioration in participants’ clinical presentation.

OTRTR therapy facilitators will receive group supervision at least once every four sessions delivered, consistent with the Forensic Matrix governance standards [18]. Facilitators will be provided with standardized recording documents to closely record the program content delivered in each session.

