### Determining progression to a full trial

There are specified criteria of success in relation to participant consent (refusal < 37%), recruitment (recruit at least 40 participants) and retention (attrition < 20% at T1). Should these criteria not be met, we would not progress to a full trial using the same design. Further feasibility outcomes have been identified as critical for the decision to pursue a future RCT of OTRTR at all. For example, if this study finds significant problems with the application of the randomization procedure (e.g., non-adherence at the participating sites), this would indicate a randomized design comparing OTRTR to any comparison treatment is not feasible and should not be pursued in this treatment setting. However, most other potential feasibility or acceptability issues found by this study could be addressed by modifying the relevant procedures in a larger RCT. If significant modifications were indicated, we would consider the need for a second feasibility trial or an embedded pilot within a full-scale RCT. Effect size estimates from this feasibility study may inform the power calculation of a future RCT only if there have been minor changes to the study design between the two studies. In this case, when calculating the necessary sample size of a future trial, we would consider both the effect sizes observed in the feasibility study (using lower bound 95% confidence interval) and the minimum clinically important difference in the primary outcomes.

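### The rules for classing Responsible Medical Officer removals do not fit together: some removals after an unwanted reaction count as randomization non-adherence, or as nothing, and not as adverse events

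*Protocol article*

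**What the plan says.** Four parts of the protocol article bear on an RMO removal.

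- **Description of the intervention, On the Road to Recovery.** The RMO may withdraw a participant from the study, and so end OTRTR sessions, "should there be a deterioration in participants’ clinical presentation". No degree of severity is attached.
- **Safety monitoring.** There are two AE routes. Route (a) applies when a "participant is removed from the study at the request of their RMO due to significant deterioration in the patient’s mental state and/or behavior". Route (b) applies when the global CORE-OM score "increases from the previous assessment to an extent that is both clinically significant and reliable". Events are recorded whatever their suspected cause.
- **Primary outcome measures, audit of adherence to randomization.** Besides actual allocation differing from assigned allocation, a removal by an RMO "who cites a reason related to the allocated condition as opposed to deterioration in clinical presentation, will also be considered non-adherence". The item adds: "Any instances of non-adherence to the randomization procedure will cause great concern". The safety item in the same list compares AE and SAE rates between the arms.
- **Determining progression to a full trial.** If significant problems with applying the randomization procedure are found, with site non-adherence as the example, "this would indicate a randomized design comparing OTRTR to any comparison treatment is not feasible and should not be pursued".

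**The concern.** The adherence rule sets two things against each other that are not opposites. Relation to the allocated condition is a cause, and deterioration is a clinical state. A removal can have both, either or neither. The AE rule then uses a stricter form of deterioration than the adherence rule and the withdrawal rule do.

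Two primary outcomes are affected. The Design section justifies AE monitoring by the potential of psychological therapies to cause harm. Yet a removal because a patient found the sessions upsetting, with no deterioration cited, would be absent from AE route (a). It would instead be logged in the randomization audit, although the allocation sequence had been followed exactly. That audit informs whether a randomized design is pursued at all.

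**Working it through.** The article states no figure on this point, so there is none to reproduce. The check is to run each kind of RMO removal through the rules as written.

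| Reason the RMO gives | AE route (a)? | Randomization non-adherence? |
|---|---|---|
| Unwanted reaction to the allocated condition, no deterioration cited | No: no significant deterioration | Yes: related to the condition, not deterioration |
| Deterioration short of significant, not linked to the condition | No: below the threshold | No |
| Deterioration short of significant, blamed on the condition | No: below the threshold | Unclear: the exemption covers any deterioration, but the reason is also condition-related |
| Significant deterioration, blamed on the condition | Yes: recorded whatever the cause | Unclear, for the same reason |
| Significant deterioration, other cause | Yes | No |
| RMO wants the other condition | No | Yes |

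The last two rows work as intended. The first three lose a possible safety event, and the first also adds to the adherence count.

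**Does AE route (b) fill the gap?** It needs a CORE-OM score to compare with the previous one. The schedule of assessments (Table 1) places CORE-OM at T0, T1 and T2 only; the weekly measures are the BIS and CSQ. Participant and data retention keeps the assessments open to people who discontinue OTRTR. The RMO rule, however, is withdrawal from the study. A participant withdrawn during treatment is therefore unlikely to have a T1 score, and route (b) is unlikely to detect the event.

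**Size.** The input is 25 participants per arm (Sample size).

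- Effect of one missed removal on the OTRTR AE proportion, if that participant has no other AE: 1/25 = 4 percentage points.
- The article gives no rate of such removals. For an assumed probability p per OTRTR participant, with independent participants, the chance of at least one among 25 is 1 − (1 − p)^25. The chance of two or more is 1 − (1 − p)^25 − 25p(1 − p)^24.

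| Assumed p | At least one of 25 | Two or more of 25 |
|---|---|---|
| 1% | 22% | 3% |
| 2% | 40% | 9% |
| 4% | 64% | 26% |
| 5% | 72% | 36% |
| 10% | 93% | 73% |

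These rates are illustrations only. They show that even a low rate gives an appreciable chance of meeting the any-instance wording at least once.

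**The case against.** Much can be said for the plan as it stands.

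- **The exemption covers any deterioration.** A reader might infer that an RMO who acts early, before deterioration becomes significant, produces a randomization failure. The text does not say that: the adherence rule exempts deterioration without a severity qualifier. This objection stands. The defect for that kind of removal is that it is unclassified or, if blamed on the condition, unclear.
- **Events are recorded whatever their cause.** A reader might infer that significant deterioration blamed on OTRTR could be filed as non-adherence and so escape the AE count. It could not. It is an AE under route (a), and nothing makes the two classes mutually exclusive. Only its adherence label is open.
- **One instance is not a verdict.** A reader might infer that a single therapy reaction would end the prospect of a randomized trial. The audit item attaches great concern to any instance, but the progression section requires significant problems. This stands too.
- **Other records exist.** SAEs are captured regardless of cause and through routine incident reporting. Withdrawals are listed with reasons, if provided, and attrition is reported by arm. Serious harm is therefore not hidden. But withdrawal reasons do not enter the AE comparison, so these records do not cure the classification.

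What the objection leaves untouched is the removal that cites an unwanted reaction with no deterioration, and the differing thresholds in the three sections.

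**Conclusion.** The point holds in a limited form. As written, an RMO removal for an unwanted reaction without deterioration is non-adherence and not an AE under route (a). A removal for deterioration short of significant is not an AE under that route and, unless also tied to the condition, is not non-adherence either. Both leave the between-arm AE comparison, and the first contributes to a criterion that the article treats as critical.

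Each such removal missed in the OTRTR arm lowers its AE proportion by 4 percentage points. This assumes 25 per arm, no other AE in that participant, and that an unwanted reaction leading to removal ought to be visible in the safety comparison. The total effect cannot be stated because no rate is given. The direction is clear only for reactions to OTRTR sessions, which TAU participants do not attend. Lesser deterioration can occur in either arm.

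The documents do not support the stronger conclusion that a harm signal automatically becomes a finding that randomization is infeasible. This is a flaw of classification that should be corrected because the correction is cheap.

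**What to change.** Reconcile the wording on deterioration in Description of the intervention, Safety monitoring and Primary outcome measures. Then give every RMO removal two independent codes, taken from the RMO's recorded reason and applied by the same definition in both arms.

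- **Safety code:** any cited deterioration or unwanted reaction, whatever its perceived cause. It enters the safety comparison by arm.
- **Adherence code:** actual allocation differing from assigned allocation, or removal because the RMO does not accept the allocation or wants the other condition. A removal citing only deterioration or an unwanted reaction is not non-adherence, whenever it occurs.

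Two simpler repairs should be avoided. Making only removals after an OTRTR session into safety events would open an AE route in one arm alone and unbalance the comparison. Counting every removal before the first session as non-adherence would score a patient who deteriorates early as a randomization failure, which the present text avoids.

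The cost is a wording change, one extra field on the withdrawal form and a possibly higher reported AE count. The coding concerns how removals are recorded and does not alter when an RMO may withdraw a participant.
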